## Methods

### Apptivate

For this project, the experiment will be conducted using the web application “Apptivate” [45], extending its initial functionally to incorporate CB algorithms connected to a routine difficulty assignment. Apptivate creates workout routines with 3 different difficulty levels, changing the total workout duration as well as rest times between exercises. PA professionals validated the routine design, ensuring that workouts match recommended guidelines for healthy adults. The overall design allows users to conduct exercises without equipment following the in-app instructions, covering different muscle groups as well as providing both warm-up and stretching exercises.

Apptivate adopts the IBC model for PA [26] as a framework for tailoring workout difficulty recommendations (ie, goals). By leveraging the IBC model, the app ensures that its recommendations address not only dynamic changes in behavior over time but also the psychological factors that influence behavior change. In particular, we capture data on the psychological constructs defined in the IBC model, which are later used as contexts for the algorithm learning process. Participants that take part in the main study will be assigned to 1 of 3 conditions:

Choice-driven: Users select their desired workout difficulty level from a predefined menu. This approach provides users with a sense of autonomy and control over their exercise routine. Choice-driven tailoring leaves the selection of the intervention to the user, allowing individuals to reveal their preferences in a participatory process [33].Data-recommended: The CB algorithm determines optimal workout difficulty (based on user data and the IBC model) and provides a recommendation to the user, but the user retains the option to choose an alternative. This design allows us to investigate the interplay between user autonomy and the effectiveness of data-driven recommendations [27].Data-driven: The CB algorithm automatically recommends workouts based on user data, including contextual features based on the IBC model, without any opportunity to opt into a different difficulty level. This method leverages a machine learning approach to personalize workout plans and potentially optimize user performance (measured as goal completion).

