### Study Design

This study poses two main hypotheses: (1) goal personalization with CBs decreases the intention-behavior gap for some users, and (2) the effectiveness of such goal personalization on behavior is mediated through individual choice. To explore these hypotheses, participants will be randomly assigned to 1 of 3 groups: choice-driven, data-recommended, or data-driven.

The target population are university students (both undergraduate and graduate) from different institutions, allowing for differences in region, language, and time zone of the participants. Randomization will be stratified by baseline demographic factors, including household composition, income, age, and gender, to ensure a representative sample within each institution. The inclusion criteria require participants to be physically healthy adults (aged older than 18 years), with access to a smartphone compatible with the mobile web application. Exclusion criteria include significant physical disabilities or medical conditions limiting exercise, based on the Physical Activity Readiness Questionnaire [46], as well as individuals actively participating in competitive sports. The participant assignment procedure will use block randomization to reduce bias and ensure even group distribution, with allocations concealed and blinded from both participants and researchers through a secure system managed by the data specialist team. Data will be stored at a secure server at the University of Concepcion, with backups of the database each hour. A deidentified version of the data and dictionary can be made available upon request.

Since there is no prior evidence regarding effect size for this study, sample size was determined using 1000 simulations, following existing guidelines [47]. Sample sizes were estimated considering the particularities of adaptive experiment design. Simulations based on the relevant populations were conducted using the epsilon-greedy algorithm. Based on simulated data, a sample size of 500 participants during 10 rounds is sufficient to evaluate differences between intervention arms and conduct statistical inference, particularly regarding demographic and behavioral characteristics between participants. The authors are currently working on a publication describing the simulations and associated power analysis, which will become available in late 2025.

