To train the reinforcement learning algorithm for the study, initial data are required for which a pilot stage was designed. In this stage, 800 participants will be recruited at one university in order to provide 1 week of activity using the app (two 3-day rounds with a rest day in between). In order to determine the sample size for the pilot, standard power calculation was assumed with a uniform distribution over 3 arms (standard randomized controlled trial). With 665 observations, the pilot is sufficient to detect differences between users. The data from round 1 will be used to estimate the optimal arm for round 2, which will be used for calibration. Participants complete a comprehensive baseline survey eliciting the IBC model as well as several other relevant characteristics (eg, time and risk preferences; see Multimedia Appendix 1) and then are assigned randomly between the 3 difficulty levels for the first round. After completion, participants are compensated for their time. Individuals can opt out from the study at any time.

During the main part of the study, 500 participants will be recruited from multiple sites expecting to participate in a medium-term challenge, completing 10 rounds, equivalent to 39 consecutive days using the app (including rest days). As noted earlier, this provides 5000 unique examples for the algorithm to determine optimal policy over time. Users will be allocated to each arm based on their baseline survey and the trained algorithm during the pilot stage. Regardless of their initial difficulty assignment, each participant will be randomly allocated with equal probability between (1) choice-driven, (2) data-recommended, and (3) data-driven arms. Participants will be compensated for their time, and there will be additional prizes using a lottery mechanism that favors (in probability) those users completing more consecutive workout routines over the course of the study. In both the pilot and main experiment, participants will stay engaged via direct email, push notifications, and social media campaigns.

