### Data Collection

Data collection in this study spans multiple dimensions, capturing individual characteristics, app usage patterns, and most importantly, user performance. This multifaceted approach allows us to provide insights on the potential heterogeneous impact of tailored goal-setting interventions.

Baseline survey: Participants will complete an online survey to gather demographic information (eg, age, gender, and socioeconomic status), fitness history (eg, frequency and type of PA), and constructs from the IBC model, such as perceived behavioral control, motivation types (autonomous and controlled), and self-regulatory capacities.Fitness app data: The app will track participant engagement and outcomes, including goal completion rates, total time spent on physical activities, and engagement metrics (eg, frequency of app interactions).Algorithm data: The CB algorithm embedded in the app will collect data on contextual features (eg, user preferences, past performance, and fitness level) and reward functions to predict optimal goals and adapt recommendations over time.

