### Statistical Analysis

Statistical analysis will focus on comparing goal completion rates, engagement metrics, and user satisfaction across the 3 intervention groups. To address missing data, a multiple imputation approach will be applied to ensure robustness in outcome estimates. The primary analysis will estimate the conditional average treatment effect for each intervention arm, with subgroup analyses to identify variations by demographics, baseline fitness, and psychological factors. Mixed-effects models will account for repeated measures and clustering within participants, while sensitivity analyses will assess the robustness of the findings under varying assumptions.

During the pilot phase, multiple CB algorithms will be evaluated based on metrics such as regret minimization (difference between actual and optimal rewards) and balance between exploration and exploitation. The main experiment will focus on estimating the conditional average treatment effect and analyzing differences in goal completion rates and engagement metrics. Subgroup analyses will explore how demographic characteristics (eg, age and gender), motivational factors, and baseline fitness levels influence responsiveness. Metrics such as cumulative reward, prediction accuracy, and contextual feature importance will be analyzed to evaluate the algorithm’s ability to personalize recommendations effectively.

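### Without a non-personalised benchmark, cumulative reward, prediction accuracy and feature importance cannot establish that the algorithm personalises

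*Protocol article*

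**What the plan says.** The first hypothesis (Study Design) is that "goal personalization with CBs decreases the intention-behavior gap for some users". The Statistical Analysis section closes with the evaluation of the algorithm: "Metrics such as cumulative reward, prediction accuracy, and contextual feature importance will be analyzed to evaluate the algorithm’s ability to personalize recommendations effectively". No reference policy is attached to these measures.

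Four other statements matter here.

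- Apptivate: the app "creates workout routines with 3 different difficulty levels, changing the total workout duration as well as rest times between exercises". Performance is goal completion.
- Data Collection: the algorithm's inputs include user preferences, past performance and fitness level.
- Study Design, pilot: participants are "assigned randomly between the 3 difficulty levels for the first round". Round 2 then uses the arm estimated from round 1.
- Study Design, main study: "each participant will be randomly allocated with equal probability between (1) choice-driven, (2) data-recommended, and (3) data-driven arms". None of these arms gives a fixed level, a random level or a bandit that ignores context.

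The protocol also plans conditional average treatment effects for the arms, subgroup analyses, success rates by difficulty level and by individual characteristics (Results), and regret for choosing among algorithms in the pilot.

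**The concern.** Tailoring difficulty can help only if the best level differs between users, or within a user over time. Statistically, difficulty must interact with context strongly enough to change which level is best. None of the three named measures isolates that.

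- **Prediction accuracy** is good whenever fitter or more motivated users complete more workouts at every level. That is prognosis.
- **Overall feature importance** flags the same prognostic variables.
- **Cumulative reward** rises if one level is easier for everyone and the algorithm steers everyone to it. A constant rule earns the same.

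Shorter workouts may well be completed more often, and past performance may well predict completion at any level, so this situation is plausible. At stake is the attribution of any benefit to tailoring, which is the mechanism named in the first hypothesis.

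**Working it through.** **1. The plan's own figures.** 500 × 10 = 5000 examples, and 10 rounds of 3 days plus 9 rest days = 39 days. Both agree with Study Design. The statement that "a sample size of 500 participants during 10 rounds is sufficient to evaluate differences between intervention arms" cannot be reproduced, because no alpha, power, effect size, completion rate or exploration rate is given. The present point does not depend on it.

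**2. Model.** For level a (easy, middle, hard) and six standard normal characteristics x:

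logit P(completion) = 0.2 + m_a + k(1.0x₁ + 0.7x₂ + 0.5x₃) + g·s_a·x₄, with s = (−1, 0, +1).

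If g = 0, every user has the same best level and tailoring can gain nothing.

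**3. Inputs.** From the protocol: three levels, 665 pilot observations with uniformly randomised level, 500/3 ≈ 167 users in the data-driven arm, 10 rounds, epsilon-greedy. Assumed: epsilon 0.10, a ridge logistic model with separate slopes per level, context constant over rounds, all effect sizes. There were 200 runs per scenario. AUC and accuracy refer to predicted completion. Importance is the fall in AUC when the characteristics are permuted.

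| Scenario (m; k; g) | Bandit reward | Uniform random | Best fixed level | AUC | Importance |
|---|---|---|---|---|---|
| A: no level effect (0, 0, 0; 1; 0) | 0.538 | 0.538 | 0.538 | 0.783 | 0.288 |
| B: level effect, no interaction (0.8, 0, −0.8; 1; 0) | 0.662 | 0.536 | 0.681 | 0.791 | 0.281 |
| B2: as B, weaker prognosis (k = 0.5) | 0.692 | 0.541 | 0.713 | 0.679 | 0.159 |
| C: as B, modest interaction (g = 0.5) | 0.661 | 0.535 | 0.676 | 0.800 | 0.283 |
| C2: as B, strong interaction (g = 1) | 0.684 | 0.533 | 0.665 | 0.815 | 0.295 |
| D: interaction only (0, 0, 0; 0; 1) | 0.690 | 0.544 | 0.556 | 0.649 | 0.172 |

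**4. Reading the named metrics.**

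- Tailoring is worthless in A, B and B2, yet AUC is 0.679 to 0.791 and importance 0.159 to 0.288.
- Accuracy tells the same story: 0.710 in A against 0.540 from always predicting the commoner outcome.
- In D, where tailoring gains most, AUC is lower than in every one of those nulls, and importance is below A and B.
- In B, reward exceeds random assignment by 0.126, in all runs. In A it shows no gain.

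**5. Adding the benchmark.** Bandit reward minus best fixed level (from unrounded values) is 0.000 in A, −0.018 in B, −0.021 in B2, −0.015 in C, +0.019 in C2 and +0.134 in D. It is positive in 0% of runs in B, B2 and C, 98% in C2 and 100% in D.

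Most of the shortfall in B is the price of exploring: 0.10 × (0.681 − 0.536) = 0.0145. The learned policy without exploration is worth (reward − 0.10 × uniform)/0.90:

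- B: (0.662 − 0.0536)/0.90 = 0.676, or −0.005 against the best fixed level
- C: (0.661 − 0.0535)/0.90 = 0.675, or −0.001
- C2: (0.684 − 0.0533)/0.90 = 0.701, or +0.036
- D: (0.690 − 0.0544)/0.90 = 0.706, or +0.150

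In C even perfect tailoring could reach only 0.680, which is 0.004 above the best fixed level. A result near zero there is therefore correct.

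**6. Arm comparison.** Take B, and assume that users in the choice arm pick the levels evenly. An untailored rule giving everyone the best level would beat choice by 0.681 − 0.536 = 0.145. Users who would have picked harder levels would gain most, so subgroup differences would also appear without tailoring.

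**7. Second simulation.** This used 800 pilot users, prognostic log-odds of 0.4 per SD for two characteristics and 0.2 for a third, and a person-level random effect of SD 0.7. AUC averaged 0.64 with no interaction, and 0.63 to 0.65 with slopes of −0.5, 0 and +0.5 across levels. A joint test of 12 difficulty-by-characteristic terms in pilot round 1 rejected in 3–5% of null trials and in 90–92% under those slopes.

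**The case against.** **The trial's main conclusion does not rest on these metrics.** This stands. The first research question compares bandits with user-chosen workouts. It is answered by randomised arms, with the conditional average treatment effect as primary analysis. A reader might infer that objective 1 would be declared met on almost any data. The protocol does not support that.

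**No pass rule is stated.** This also stands. The list is open-ended and sets no threshold, so one cannot say that a useless algorithm would be declared effective.

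**A condensed article may leave the benchmark to the analysis plan.** This is fair as to detail. But the article itself names the measures and their purpose, and the objection is that they do not serve it.

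**The metrics may be meant differently.** Accuracy is not defined, and importance could mean which features drive the recommendation. Even so, that shows what the algorithm used, not whether using it raised completion.

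**Cumulative reward is not always favourable.** Correct: in A it shows no gain, so it can count against the claim. Saying that all three metrics flatter a useless algorithm in every case would be too strong.

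**Other analyses partly cover the gap.** Success rates by difficulty and by characteristics are planned, but not stated as an interaction, and in the main study difficulty is chosen or algorithm-assigned. Regret is named for choosing algorithms in the pilot. Its wording also differs: Contextual Bandits Algorithm refers to the recommended action on both sides, while Statistical Analysis sets actual against optimal reward.

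**A pilot interaction test should not decide the matter.** Agreed. One three-day round at one university precedes most in-app history and cannot show adaptation within a user over time.

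**Conclusion.** The point holds for the attribution to personalisation only. As named, accuracy and overall importance cannot separate prognosis from tailoring, and cumulative reward cannot separate tailoring from steering everyone to an easier level. In the simulations, scenarios where tailoring gained nothing gave AUC up to 0.791 and reward gains of 0.126 to 0.151 over random. Setting reward against the best single level separated these from strong interaction.

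The sizes rest on assumed effects, epsilon 0.10, static context and learning from the pilot plus one arm (1,670 rows rather than 5000). The direction for accuracy and importance was the same in every null setting tried that had prognostic characteristics. In the second simulation, AUC above 0.55 became rare (2–9% of trials) only when no characteristic was prognostic.

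The randomised comparison of goal completion stands as planned. It can show that an algorithm-driven arm beats choice, but not that tailoring is the reason. This is a worthwhile, inexpensive improvement, not a flaw in the primary analysis.

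**What to change.** In Statistical Analysis, keep the three metrics as descriptive monitoring and name the following as the evidence on personalisation.

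1. **Policy contrast.** Estimated completion under the learned contextual policy, without exploration draws, minus that under the best single difficulty level for all users, with a participant-level confidence interval. Estimate it by cross-fitting on randomised pilot round 1, choosing both the policy and the best level in the training folds. Where assignment probabilities are logged, repeat it on the data-driven arm of the main study, so that time-varying context is covered.
2. **Supporting evidence.** A joint difficulty-by-characteristic interaction test on pilot round 1, reported beside the contrast and not as a gate on the claim.

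The two regret descriptions should also be aligned.

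**Cost.** A little more analysis of data already collected or logged, no extra participants, and a personalisation claim that is harder to make. Two cautions apply. In the second simulation a one-sided cross-fitted test of the policy contrast rejected in 2–4% of null trials when levels differed, but in 10–12% when all levels were equal, so its interval should be checked by simulation and read with the interaction test. With epsilon 0.10, each non-preferred level has probability 0.10/3 ≈ 0.033 and an inverse-probability weight of 30, so main-study estimates may be imprecise. The pilot analysis is already under way, so the text should state whether these analyses were fixed before its interaction results were seen.

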### Ethical Considerations

Our study is considered an adaptive experiment or adaptive intervention trial [30,31]. Unlike a randomized controlled trial, sampling is not fixed, but instead each round is controlled by a recommendation algorithm, as noted in the previous section. As such, based on institutional guidelines, this study does not meet the criteria for a clinical trial. The Ethics, Bioethics, and Biosafety Committee of the Vice Presidency of Research and Development at the University of Concepción has reviewed our study under Project Fondecyt (11240325), titled “Tailored goals versus individual choice: a field experiment on commitment devices for health behavior,” submitted in the Fondecyt Initiation 2024 Call by [name] [name], as the lead researcher and faculty member at the School of Engineering at the University of Concepción. The Committee has confirmed that it meets the ethical and bioethical standards and procedures established nationally and internationally for research involving human participation. Although this protocol does not correspond to a clinical trial, we included a SPIRIT (Standard Protocol Items: Recommendations for Interventional Trials) checklist to facilitate study implementation (Multimedia Appendix 2).

## Results

This research is supported by the Fondecyt Initiation Grant 2024 (grant ANID 11240325; funding period 2024-2026). The pilot was conducted in September 2025. Data analysis for the pilot is undergoing, and the main study is planned for early 2026. Preliminary results from the pilot data will be available in November 2025. Our main statistical analysis includes a direct comparison (paired tests) between success rates across intervention arms, as well as by difficulty level and individual characteristics. We anticipate publishing the findings in late 2026. Dissemination will be conducted simultaneously via a web-based seminar for all participant institutions during 2026.

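### Paired tests are named for comparing three independent randomised arms, where no pairs exist, and this does not line up with the primary analysis in the Statistical Analysis section

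*Protocol article*

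**What the plan says.** In the protocol article, the Abstract (Results paragraph) and the Results section carry the same sentence: "Our main statistical analysis includes a direct comparison (paired tests) between success rates across intervention arms". It goes on to list difficulty level and individual characteristics as further comparisons.

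The design is described in three places:
- Apptivate: "Participants that take part in the main study will be assigned to 1 of 3 conditions".
- Study Design, on the method: "The participant assignment procedure will use block randomization to reduce bias and ensure even group distribution". The randomisation is also said to be stratified by baseline demographic factors.
- Study Design, on the main study: "each participant will be randomly allocated with equal probability between (1) choice-driven, (2) data-recommended, and (3) data-driven arms".

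The Statistical Analysis section states: "The primary analysis will estimate the conditional average treatment effect for each intervention arm". It adds: "Mixed-effects models will account for repeated measures and clustering within participants". It does not mention paired tests.

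**The concern.** A paired test needs a defined link between an observation in one arm and an observation in another: the same person under both conditions, or two people matched by design. The article describes neither. Blocking and stratification balance the arms, but they do not create one-to-one pairs.

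Two things are at stake. First, anyone implementing the sentence literally must invent a pairing unit, and the error rate of the main between-arm comparison depends on that choice. With 10 rounds per participant, the round is an easy unit to pick. Pairing by round drops the variation between participants, which is the error term that the randomisation supports. Second, one part of the article calls paired comparisons the main analysis and another calls a conditional average treatment effect primary. A reader cannot tell which result answers the first research question, the comparison of the bandit algorithm with user choice.

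**Working it through.** **Step 1. Is there a pair?** Apptivate and both allocation statements in Study Design place each participant in one of three arms. Nothing describes switching arms, re-randomisation between arms or matching. The Results sentence lists difficulty level separately from intervention arms, so the arms in that sentence are the three randomised groups. One participant may contribute rounds at several difficulty levels, so pairing within a person is possible for that comparison. It is not possible across arms.

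**Step 2. The plan's own figures.** Study Design says "a sample size of 500 participants during 10 rounds is sufficient to evaluate differences between intervention arms", and later "this provides 5000 unique examples for the algorithm to determine optimal policy over time". The count agrees: 500 × 10 = 5000. Per arm, 500 / 3 = 166.7; with the 20% maximum dropout given under Anticipated Findings, 500 × 0.8 / 3 = 133.3. The figure of 500 participants cannot itself be reproduced, because the article gives no effect size, success rates or within-participant correlation and refers to a separate publication for the simulations.

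**Step 3. Type I error under different pairing units.** The documents give 10 rounds and about 166 participants per arm. Assumptions, not in the documents: 50% completion, within-participant correlation (ICC) of 0.05 to 0.5, two-sided 5% level. Trials with no arm difference were simulated, 4000 per setting, with beta-binomial participants and a small round effect common to both arms.

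| Test | ICC 0.05 | 0.1 | 0.3 | 0.5 |
|---|---|---|---|---|
| Unpaired (Welch) on participant completion rates | 0.050 | 0.049 | 0.051 | 0.044 |
| Paired t, participants paired arbitrarily | 0.049 | 0.051 | 0.050 | 0.044 |
| McNemar, arbitrary pairs, one round | 0.049 | 0.052 | 0.052 | 0.050 |
| Paired t on the 10 round-level arm rates | 0.102 | 0.164 | 0.360 | 0.513 |
| Unpaired pooled z-test on all rounds, clustering ignored | 0.100 | 0.164 | 0.318 | 0.402 |

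**Step 4. Analytic check of round-level pairing.** Write n for participants per arm, p for the completion rate and ρ for the ICC. The true variance of the mean difference over 10 rounds is (2p(1−p)/n) × [ρ + (1−ρ)/10]. The paired t-test sees only the spread between rounds, so it estimates (2p(1−p)/n) × (1−ρ)/10. The ratio of true to estimated variance is 1 + 10ρ/(1−ρ), and n and p cancel. The rejection rate is then about P(|t₉| > 2.262/√ratio):
- ρ = 0.05: ratio 1.526; 2.262/1.235 = 1.831; 0.100
- ρ = 0.1: ratio 2.111; 2.262/1.453 = 1.557; 0.154
- ρ = 0.3: ratio 5.286; 2.262/2.299 = 0.984; 0.351
- ρ = 0.5: ratio 11.0; 2.262/3.317 = 0.682; 0.512

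This agrees with the simulation. Because n cancels, more participants would not reduce the inflation.

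**Step 5. Source of the inflation.** The unpaired pooled test in the last table row is also inflated. Its design effect is 1 + 9ρ, which is 1.45, 1.9, 3.7 and 5.5, giving approximate rejection rates of 0.104, 0.155, 0.308 and 0.403. The damage therefore comes from leaving out between-participant variation, and pairing by round is one way of doing that.

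**The case against.** A reader might infer that the main p-values would be invalid whatever was done. The documents do not support that. The pairing unit is not stated, and arbitrary pairing of participants on their own completion rates holds its level (0.044 to 0.051). The inflated rates need a further step, ignoring clustering, and the Statistical Analysis section says that clustering will be modelled. They also rest on an assumed completion rate and assumed correlations. All of this stands, and it limits the claim.

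The phrase may also be loose wording for pairwise tests, since three arms are naturally compared two at a time. That is plausible. The text would still name the wrong procedure in two prominent places, and the correction would be the same.

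A reader might also infer a flat contradiction over the primary analysis. That goes too far. The Abstract and Results say that the main analysis includes these tests, not that it consists of them. The Statistical Analysis section itself lists treatment-effect estimation alongside differences in completion rates. A treatment effect, a mixed model and arm contrasts can belong to one analysis. What remains is that the article does not join them, and that only one of the descriptions uses paired tests.

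Arbitrary participant pairing is not a good rescue either. Its p-value changes with the order in which participants are listed, 500 does not divide equally by three, and dropout would leave some participants without a partner.

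**Conclusion.** The point holds in limited form. The article names paired tests for a comparison between independent parallel arms in which no pairs are defined, and this wording is not aligned with the Statistical Analysis section. The design mismatch and the misalignment follow from the text alone.

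The size is conditional. Type I error is near 5% if participants are paired arbitrarily, and about 10% to 51% if arm rates are paired by round, for an ICC from 0.05 to 0.5 with 50% completion and 166 per arm. These figures show what an undefined pairing unit could permit. They do not predict what the investigators will do, given the planned mixed-effects models.

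**What to change.** In the Abstract and in Results, replace the paired tests with pairwise between-group (independent-arm) comparisons of goal completion, taken from the participant-clustered mixed-effects model already in the Statistical Analysis section. Describe the primary analysis in the same terms in all three places, saying how the arm comparisons relate to the conditional average treatment effect. If paired methods are wanted, keep them for within-participant comparisons such as difficulty level, and say so.

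The cost is wording only, with no extra participants or data. The main study is described as planned for early 2026, after the pilot, so on that timetable the change can be made before any main-study outcomes are seen. Covariate lists, the choice between mixed model and GEE, and the rank given to conditional effects can be left to the analysis plan; this point does not depend on them.
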